### Treatment interventions

The randomization process allocates eligible patients to one of the two surgical treatment groups. Surgical options, according to the guidelines for the surgical management of AEDH [7], consist of the evacuation of the hematoma with a craniotomy, or with additional DC, leaving a large bone flap [3]. However, the bone flap must be replaced and secured with a fixation system (plates and screws) in patients who received a craniotomy. It is essential that all treatments for surgical management of AEDH are consistent within the two groups, including preoperative preparation and anesthesia. The only difference between the two arms will be represented by the removal or replacement of the bone flap. To provide well-established surgical techniques and a standardized surgical treatment is the essential aim of this study. The operation will be performed by a qualified senior neurosurgeon within each of the participating centers.

The post-operation management process and the medical decisions concerning the patients will not be affected by their recruitment into the PREDICT study. All patients will receive postoperative care management according to the guidelines and intensive care protocols, including radiographic or biochemical examination. Normally, a cranioplasty is recommended to reconstruct the skull in patients who underwent DC. The treatment in case of complications will differ considerably between patients, according to their clinical manifestations (epilepsy or cerebral infarction, or late complications as hydrocephalus).

### Aims and outcomes

The trial aims to evaluate craniotomy and DC on AEDH patients in terms of efficacy, economic benefits, and complications. The primary endpoint is the Glasgow Outcome Score-Extended (GOSE) at 6 months post-injury, the most commonly used prognostic evaluation scale in TBI, which allows the assessment of the long-term functional outcomes, including overall mortality and morbidity rates [8, 9].

Additionally, the following secondary endpoints are intended to be investigated as supplementary functional and cognitive measures:
The incidence of postoperative cerebral infarction within 6 months post-injury, to be primarily diagnosed by independent radiologists by CT or MRI examinationThe incidence of additional craniocerebral surgery, as a result of clinical deterioration after initial surgical treatment for AEDH, within 6 months post-injuryThe incidence of serious adverse events (SAE) within 6 months post-injury, and SAE is defined as an untoward occurrence that:
Results in deathIs life-threateningRequires hospitalization or prolongation of existing hospitalizationResults in persistent or significant disability or incapacityIs otherwise considered medically significant by the investigatorThe length of patient’s stay in ICU and hospital after initial surgery within 6 months post-injuryDetailed economic evaluation, defined as the total medical expenses related to the treatment for AEDH, including the costs of operations, hospitalization, and rehabilitation within 6 months post-injuryQuality of life at 6 months post-injury with the score of 5-level EuroQol Five Dimensions Questionnaire (EQ-5D-5L). The EQ-5D is a generic instrument to describe and evaluate the health condition on the basis of five dimensions: mobility, self-care, usual activities, pain/discomfort, and anxiety/depressionMMSE (Mini-Mental State Examination) scores at 6 months post-injury

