## Background

Traumatic brain injury (TBI) represents the most challenging global public health care issues, with more than 50 million people suffering from TBI each year worldwide [1, 2]. Acute epidural hematoma (AEDH), a common and severe type of TBI, occurring approximately in 2 to 4% of all TBI patients [3–5], accounts for a substantial proportion of fatal head injuries, with mortality ranging from 1.2 to 33%. AEDH befalls more frequently in young people, with a mean age between 20 and 40 years. Elderly people rarely suffer from AEDH but have a significantly higher mortality. Vehicle-related accidents are the main cause of AEDH, accounting for 53% of all cases (range, 30–86%). Other causes of AEDH, including falls, assaults, and sports injuries, have been reported in several studies [3–5].

Epidural hematomas are caused by bleeding between the outer layers covering the brain and the inner table of the skull. The rapid rise of intracranial pressure (ICP), caused by the mass effect, will result in midline shift and direct or indirect compression of the brainstem. This condition represents a potentially life-threatening emergency and requires prompt diagnosis and neurosurgical intervention. The large availability of computed tomography (CT) scanners for internal examinations facilitates the fast diagnosis of AEDH and allows the monitoring of the disease progression. Thus, the expeditious surgical evacuation of AEDH is an attainable gold standard and is often expected to have a good clinical outcome. Indeed, the treatable nature of epidural hematomas (EDH) has led some surgeons to suggest a “toward zero mortality” as an achievable target for this condition.

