### Data analysis

Patient characteristics and variations in both treatments and outcomes will be defined using descriptive statistics. Continuous variables will be described as mean and standard deviation (SD) or as median and interquartile range (IQR). To assess the differences between cohorts, appropriate tests will be performed according to the distribution and scale of measurement. Student’s t-tests or Mann-Whitney U tests will be used for continuous variables, and *X*^*2*^ tests or Fisher’s exact test will be used for categorical variables. Exploratory analyses on AEDH will be performed, aiming at understanding the complexity of the disease and to discover new possible associations. In addition to standard descriptive statistics, multivariable regression models or other analyses may be used if appropriate. *P* < 0.05 will be considered to be statistically significant. Factors such as age, the severity of injury, and the timing of injury will be included as covariates in the primary analysis, with the center considered as a random effect.

More specifically, the outcome measures will be assessed using the GOSE, an ordinal scale. The GOSE categories of death, vegetative state, lower severe disability, and upper severe disability will be considered as unfavorable outcomes. Favorable outcomes will be defined by following the GOSE categories: lower moderate disability, upper moderate disability, lower good recovery, and upper good recovery. However, GOSE conventional analysis usually dichotomizes the ordinal scale into a binary scale, and this may discard a lot of relevant information, reducing both the outcomes’ clinical relevance and the statistical efficiency of the analysis. Ordinal logistic regression analysis will be used to quantify the prognostic effects across the full range of the GOSE. And the final effect will be a pooled estimate of the common odds ratio. Additionally, a secondary analysis will be reported for the two pre-specified binary outcomes: dead versus alive and unfavorable versus favorable outcomes.

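### ICU and hospital length of stay is tested as a plain duration, so early in-hospital deaths enter as short stays and bias this secondary comparison if early mortality differs between arms

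*Protocol article*

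**What the plan says.** Aims and outcomes lists, among the secondary endpoints, the length of "stay in ICU and hospital after initial surgery within 6 months" post-injury. It is defined as a duration, with no rule for a patient whose stay ends in death. The same list contains an economic evaluation: "total medical expenses related to the treatment for AEDH, including the costs of operations, hospitalization, and rehabilitation within 6 months" post-injury.

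Data analysis sets the tests by type of variable. Student's "t-tests or Mann-Whitney U tests will be used for continuous variables". Length of stay is not named there, and the section adds that "multivariable regression models or other analyses may be used if appropriate".

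Death is handled explicitly elsewhere. On the primary scale, "The GOSE categories of death, vegetative state, lower severe disability, and upper severe disability will be considered as unfavorable outcomes". A further analysis is planned for "dead versus alive and unfavorable versus favorable outcomes". Death is also one of the criteria for a serious adverse event. For the disease in general, Background describes acute epidural hematoma "with mortality ranging from 1.2 to 33" percent.

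**The concern.** Scores such as EQ-5D-5L or MMSE are missing after death. Length of stay is not: the value exists, and it points the wrong way. A patient who dies on day 2 has a genuine stay of 2 days, and a t-test or Mann-Whitney test of the duration treats this like a survivor's quick discharge.

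The patients have brain herniation, so some deaths are to be expected, and the trial asks whether the two operations differ in outcome. If craniectomy prevents some early deaths, the craniotomy arm would gain artificially short stays, and the reverse holds if craniectomy causes them. Because the trial aims include economic benefit, a shorter stay is likely to be read as an advantage.

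**Working it through.** **Inputs from the article.** Total 120, allocation 1:1, so 60 per arm. With the planned 10% loss, 60 × 0.90 = 54 per arm. Significance is 5% two-sided, so 2.5% in each direction. Planned favourable rates of 93% and 72% (Sample size calculation) imply unfavourable rates of 7% and 28%. Unfavourable includes vegetative state and severe disability, so expected mortality by arm lies below these figures. The article states no figure for the bias, so there is none to reproduce.

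**Assumptions.** Underlying stay is lognormal, median 20 days, log-SD 0.6, the same in both arms. Time to in-hospital death is lognormal, log-SD 0.8, median 3, 7 or 14 days. Stay is cut at death. Mortality by arm is varied.

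**Effect on the mean.** The mean of a lognormal is median × exp(σ²/2). Underlying stay: 20 × exp(0.18) = 23.9 days. Deaths at median 3 days: 3 × exp(0.32) = 4.1 days. The arm difference is about (mortality difference) × (23.9 − 4.1): 0.10 × 19.8 = 2.0 days at 15% versus 5%, and 0.15 × 19.8 = 3.0 days at 20% versus 5%.

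**Closed-form limit for Mann-Whitney.** If every death came before every survivor's discharge, the chance that a random patient in the deadlier arm has the shorter stay would be 0.5 + (d₁ − d₂)/2. Its null standard error is √[(2n+1)/(12n²)] = √[109/(12 × 54²)] = 0.0558.

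- 15% versus 5%: 0.55, z = 0.05/0.0558 = 0.90, wrong-direction rate P(Z > 1.96 − 0.90) ≈ 14%.
- 20% versus 5%: 0.575, z = 0.075/0.0558 = 1.34, rate P(Z > 1.96 − 1.34) ≈ 27%.
- Equal mortality: 0.50, rate 2.5%.

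Deaths that overlap survivors' stays reduce these rates.

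**Simulation.** 4,000 trials per scenario; the table shows the percentage significantly favouring the deadlier arm.

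| Mortality | Test | Death median 3 d | 7 d | 14 d |
|---|---|---|---|---|
| 5% v 5% | Mann-Whitney | 2.6 | 2.7 | 2.3 |
| 10% v 2% | Mann-Whitney | 10.7 | 7.4 | 5.0 |
| 15% v 5% | Mann-Whitney | 13.0 | 9.7 | 6.9 |
| 20% v 5% | Mann-Whitney | 22.6 | 17.8 | 10.1 |
| 15% v 5% | t-test | 10.1 | 6.8 | 5.4 |
| 20% v 5% | t-test | 15.8 | 12.6 | 8.2 |

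A separate simulation with survivors' stay at median 21 days, log-SD 0.7, and deaths at median 3 days gave 12.7% and 23.2% for the 15% v 5% and 20% v 5% cases with Mann-Whitney.

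**Outer bound.** If every planned unfavourable outcome were a death (28% versus 7%), Mann-Whitney gives 43.0%, 30.4% and 15.4%. This is an extreme and not a forecast.

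**With in-hospital deaths ranked worst.** The same Mann-Whitney test favours the deadlier arm in 0.5% of trials or fewer in every unequal-mortality scenario. With equal mortality each direction stays near 2.5%.

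**The case against.** The strongest reply is that the article never says a death counts as a short stay. It does not say who enters the comparison, the rule for continuous variables is general, and other analyses are allowed. A Mann-Whitney test with deaths ranked worst would not contradict the text. The scoring of deaths in a secondary endpoint may also be written in a full protocol or analysis plan that is not shown. This has weight: it limits the point to what follows if the article is applied literally. It does not remove the point, because the article does fix a plain duration and a pair of tests. Under that definition a stay ended by death is an observed short value, and ranking it worst would be a different endpoint that the article does not describe.

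A reader might infer that the trial as a whole could declare the deadlier arm better. The documents do not support that. Death is a category of the primary GOSE outcome, dead versus alive is compared separately, and deaths count as serious adverse events. Only the stay comparison can mislead, and only if read alone.

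A reader might also take the 33% top of the Background mortality range as a planning case for one arm. It exceeds the 28% unfavourable rate that the sample-size section implies for craniotomy. It also describes the disease in general, whereas this trial limits age to 18–65 and excludes injuries judged unsurvivable.

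On cost, the objection largely stands. An early death really does cost less, so the value is not mis-scored. What remains is interpretation, and the mortality and GOSE results needed for it are already planned.

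**Conclusion.** The point holds for one secondary endpoint. Applied as written, the stay comparison is biased toward the arm with more early deaths. At 15% versus 5% mortality the Mann-Whitney wrong-direction rate is about 7 to 13%, and at 20% versus 5% about 10 to 23%, against 2.5% nominal. The t-test is affected somewhat less.

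These sizes rest on assumed stay distributions, death times and arm mortalities, none of which the article gives, and on the same underlying stay in both arms. The bias shrinks when deaths come late and vanishes when mortality is equal. The direction follows from the endpoint definition whenever in-hospital deaths are more frequent in one arm and come before those patients would have been discharged.

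**What to change.** State how in-hospital deaths enter the comparison. The simplest form is to compare ICU and hospital stay in all randomised patients by the Mann-Whitney test, with in-hospital deaths given the worst rank. An alternative is days alive and out of hospital, and out of ICU, to 6 months post-injury. Under that alternative a patient who is discharged and dies later keeps the days actually spent alive and out; scoring every death as zero would contradict the definition. The t-test should not be used on worst-rank scores, because its result would depend on the arbitrary value assigned to death.

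Show raw stay descriptively, separately for survivors and for those who died. Interpret the cost difference only beside mortality and GOSE.

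The cost is small but not nil. The endpoint then mixes survival with stay and counts deaths again alongside GOSE, which is why raw stay must be shown too. Data collection names hospital admission and the times of injury, emergency room arrival, CT and surgery, but not discharge or death dates. Their availability on the case report form or from serious adverse event reports must be confirmed. Recruitment began in September 2020, so the change should be documented as an amendment or in the analysis plan before outcomes are compared by arm.

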### Data collection

Once patients are enrolled in the study, data related to demographic and clinical information, including hospital admission, treatment process, and follow-up, will be collected by the local investigators and recorded on the case report form (CRF). Detailed data consisting of neurological condition, timing of injury (also the ER, initial CT, and surgical operation), radiographic abnormalities, operation data, and postoperative care management (including ICP management and pharmacological data) will also be recorded. Postoperative CT scan will be performed routinely on the 1st, 3rd, and 7th day post-initial surgery. Cerebral infarction will be initially detected by postoperative CT image depicting a low-dense area. The blood supply of involved lobes will be further detected by transcranial Doppler sonography (TCD) and/or MR. Follow-up visits in the outpatient department are scheduled at 1, 3, and 6 months after injury; data will be collected and recorded. The information recorded on CRFs will be entered into an electronic data collection (EDC) database by a designated person within each participating center. A subject must be withdrawn from the trial if one of the following applies:
Each patient or his/her legally authorized representative has the right to require withdrawal from the study cohort for any reasons after enrollment.The investigator will withdraw a patient who is randomly allocated to a craniotomy and that eventually requires a DC as lifesaving action during the initial surgery.In addition, the investigator could withdraw the patients from their allocated treatment group if a clinical reason for not performing the surgical intervention is identified after randomization.Lost to follow-up.

The primary reason for all discontinuations and withdrawals will be documented.

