### Sample size calculation, randomization, and blinding

Our data and results from a previous retrospective study are showing that almost all the patients who received a synchronous DC (93%) had a GOSE of 6.63 ± 1.27, with a favorable outcome (defined by the GOSE categories: lower moderate disability, upper moderate disability, lower good recovery, and upper good recovery). Patients who received craniotomy had a GOSE of 5.78 ± 1.58, with a favorable outcome in 72% of the patients [6]. We calculated the sample required in this clinical trial with a significance level of 5% (two-sided) and a power of 80% to demonstrate the difference in the rate of favorable outcome, with an assumption that 10% of the patients would be lost during follow-up. Ultimately, considering the quality of the study, the sample size is enlarged to 120.

All participating centers must have a neurosurgical on-call team and an emergency department responsible for the admission of head-injured patients to identify eligible patients. After recording the patient’s clinical information, including Glasgow Coma Scale (GCS), pupillary reactivity, and CT findings, an electronic data collection (EDC) database will generate the subject identification number that will be allocated to the eligible patients. A secure central web-based randomization management information system will be used for the randomization of eligible patients. The system will provide an immediate allocation along with the patient randomization record number for the trial, and individual randomization record numbers can be checked at any time. Blocked randomization will be used, with a block size of 4 and an allocation ratio of 1:1. The 24-h central web-based randomization management information system will be backed by one delegated person (available 24 h per day) who will assure the cover-up of the record allocation. The delegated person responsible for randomization will not be involved in the treatment procedure. A confirmatory email will be sent to the investigator of each center involved to verify the allocation.

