A patient who is randomly allocated to the craniotomy group, but finally receives a decompressive craniectomy as a lifesaving action during the initial surgery, will be rejected from this randomized controlled trial. This potential selection bias is beyond the control of the investigators, and according to the current guidelines, no specific surgical options are provided for the enrolled participants. Nevertheless, patients’ detailed data will be recorded, providing the observational cohort information necessary to further analyze the possible factors and potential bias.

Due to the nature of the intervention, and the risk that DC surgical procedure will result in skull defect, patients and treating doctors cannot be blinded to allocation. However, the evaluators involved in this study and the investigators responsible for the outcomes’ analysis are blinded to the groups.

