Best efforts will be made to contact the next of kin during the treatment and seek their approval to the patient’s inclusion within the trial. Views of withdrawal to enter or continue the trial from next of kin will be respected, and no further data will be collected from the patient.

If participants regain their decisional capacity during the procedure, they will be given information about the trial and their consent will be sought to continue in the trial. Meanwhile, participants or next of kin are also informed that they could withdraw consent and quit at any moment during trial, without affecting their treatment process, only by informing the investigator on their willingness to keep their collected data for future analysis or delete them.

No patients or the public were directly involved in the design or conduct of the study. The patients and their caregivers will be informed about the whole duration of the study (4 years), and any development may occur during the process. The trial results will be disseminated through academic conferences and published in peer-reviewed journals. In case of publication, the investigators will immediately inform the patients and their caregivers by telephone or e-mail.

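### Loss to follow-up is made a mandatory withdrawal from the trial, which as written takes about 10% of randomised patients out of the comparison and leaves their earlier GOSE unused

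*Protocol article*

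**What the plan says.** All references are to the protocol article.

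- **Data collection.** The rule is mandatory: "A subject must be withdrawn from the trial if one of the following applies". Four items follow: withdrawal at the request of the patient or representative; a craniotomy patient who needs DC during the initial surgery; a clinical reason, found after randomisation, for not performing the operation; and "Lost to follow-up".
- **Sample size calculation, randomization, and blinding.** The second of these items is also described here: such a patient "will be rejected from this randomized controlled trial". The data are not thrown away: "patients’ detailed data will be recorded, providing the observational cohort information" needed for later analysis.
- **Same section.** The calculation assumes that "10% of the patients would be lost during follow-up", and the total is set at 120, allocated 1:1. The planning rates of favourable outcome are 93% (DC) and 72% (craniotomy).
- **Data collection and Table 1.** "Follow-up visits in the outpatient department are scheduled at 1, 3, and 6 months after injury". Table 1 schedules GOSE in the period up to discharge and at each of these visits.
- **Aims and outcomes; Data analysis.** The primary endpoint is GOSE at 6 months, analysed by ordinal logistic regression. Favourable versus unfavourable is a secondary binary analysis.
- **Ethics and dissemination.** When consent is withdrawn, participants or next of kin state their "willingness to keep their collected data for future analysis or delete them".

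**The concern.** Loss to follow-up is a missing outcome. It is not a change in whether a patient was randomised. The rule treats it as a change of trial status and lists it beside a group that the article removes from the randomised trial. Nothing in the article says that patients lost to follow-up stay in the analysis set, so a reader who applies the text literally would analyse only those seen at 6 months.

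That selects patients on an event after randomisation. If the chance of being lost depends on recovery, and does so differently in the two arms, the arms are no longer comparable. Many of these patients will also have an earlier score on the primary scale, at discharge, 1 month or 3 months, and the literal rule leaves that information unused in the randomised comparison.

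A later analysis plan may choose a missing-data method, but it would then be imputing outcomes for patients whom the protocol says have been withdrawn from the trial. The protocol wording therefore has to be settled first.

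**Working it through.** **1. What withdrawal means in this list.** For the craniotomy-to-DC item, Data collection uses withdrawal and the sample-size section uses rejection from the randomised trial, for the same patients. That is the only place where the article says what withdrawal under this list means for the randomised comparison. Loss to follow-up falls under the same introductory sentence with no separate explanation.

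**2. How many patients.** Planned loss is 10% of 120 = 12. Expected unfavourable outcomes with 60 per arm:

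- DC: 60 × (1 − 0.93) = 4.2
- Craniotomy: 60 × (1 − 0.72) = 16.8
- Total: 21

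The number with unknown outcome is thus more than half the expected number of unfavourable outcomes.

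**3. The plan's sample size, and power.** With pooled variance, two-sided 5%, 80% power and mean rate (0.93 + 0.72)/2 = 0.825:

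- n = [1.960 × √(2 × 0.825 × 0.175) + 0.842 × √(0.93 × 0.07 + 0.72 × 0.28)]² / 0.21² = (1.053 + 0.435)² / 0.0441 ≈ 50.2, so 51 per arm or 102 in all.
- With 10% loss: 102/0.9 = 113.3, so 114.

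The article does not state its calculated number before enlarging to 120, so there is no exact figure to reproduce; 114 is compatible with that enlargement. Power with n per arm is Φ[(0.21√n − 1.053)/0.516]:

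- 54 per arm (12 lost): Φ(0.949) = 82.9%
- 60 per arm: Φ(1.110) = 86.7%

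Losing 12 patients therefore keeps power for the binary outcome above the planned 80%. Using the earlier GOSE could recover at most the gap of about 4 points.

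**4. Extreme bounds.** Assume that observed patients show 93% and 72%, and let every lost patient take the outcome least or most favourable to DC.

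| Lost (DC, craniotomy) | Lower bound | Upper bound |
|---|---|---|
| 6, 6 | (54×0.93)/60 − (54×0.72 + 6)/60 = 8.9 points | (54×0.93 + 6)/60 − (54×0.72)/60 = 28.9 points |
| 3, 9 | (57×0.93)/60 − (51×0.72 + 9)/60 = 12.2 points | (57×0.93 + 3)/60 − (51×0.72)/60 = 32.2 points |
| 9, 3 | (51×0.93)/60 − (57×0.72 + 3)/60 = 5.7 points | (51×0.93 + 9)/60 − (57×0.72)/60 = 25.7 points |

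**5. Direction.** Suppose the true difference is 21 points, loss in the DC arm is unrelated to outcome, and loss in the craniotomy arm depends on 6-month outcome. The loss rates are assumed.

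- Poor outcome lost at 30%, good at 5%: the observed craniotomy rate is (0.72×0.95)/(0.72×0.95 + 0.28×0.70) = 0.684/0.880 = 77.7%, so the difference shrinks to 15.3 points.
- Good outcome lost at 20%, poor at 5%: (0.72×0.80)/(0.72×0.80 + 0.28×0.95) = 0.576/0.842 = 68.4%, so the difference grows to 24.6 points.

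If loss depends only on 3-month status, the bias is smaller. With a bivariate normal latent scale, a 3- to 6-month correlation of 0.70 to 0.85 and a 3-month favourable rate of 55% to 72% in the craniotomy arm (all assumed), the two cases give 17 to 18 points and about 23 points. Either sign is possible.

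**The case against.** The strongest reply is that withdrawal is neither deletion nor exclusion from analysis. The list stands under Data collection and can be read as a record of how participation ends. Where the article describes the data of patients who leave, it points to retention: crossover data are recorded, refusal by next of kin stops further collection only, and deletion follows only from an expressed wish. The word rejected is applied to crossovers alone. A reader might infer that the rule forces a complete-case primary analysis and discards the 1- and 3-month GOSE. The article says neither, and nothing in Data analysis bars imputation or use of earlier scores. This part of the reply stands, and it limits the point to what the wording says and permits.

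The absence of a named missing-data method is likewise no fault, since that may sit in an analysis plan.

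Other parts of the reply also stand:

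- The 8.9 to 28.9 range would arise from any 10% missingness. A wording change alone does not narrow it.
- A reader might infer that loss will be heavier among well-recovered craniotomy patients, because DC patients return for cranioplasty. The article only says that cranioplasty is normally recommended, without timing or place, so neither unequal loss nor its direction is established.
- Adjusting for 3-month GOSE removes the bias completely only when loss depends on nothing else and the 3-month score is available. Patients lost sooner will lack it.
- Power is not harmed.

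What the reply does not remove is the mandatory rule itself. It is stated text. Its only explained neighbour in the list means removal from the randomised trial, and nothing in the article exempts patients lost to follow-up.

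**Conclusion.** The point holds as a defect in a stated rule. Read as written, the article takes patients lost to follow-up out of the randomised comparison: about 12 of 120 at the planned loss, against about 21 expected unfavourable outcomes. Their GOSE up to 3 months is then left unused.

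Bias follows only if loss depends on recovery and differs by arm, and its direction cannot be known in advance. With 6 lost per arm and 93% versus 72% among those observed, the limits around the 21-point difference are 8.9 and 28.9 points. These are extremes, not expected errors. The assumed loss patterns in the working move the difference by about 2 to 6 points, either way. All these figures concern the binary outcome used for planning; no figure has been derived for the common odds ratio of the ordinal analysis.

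The change should be made, because it is cheap and removes a conflict between the protocol and any sound handling of missing outcomes.

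**What to change.** In Data collection, remove loss to follow-up from the mandatory withdrawal list, or state that it only records that contact has ended. Then state that:

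- these patients remain in their randomised arm in the primary analysis set;
- any death known from any source counts as GOSE 1;
- the GOSE already collected up to discharge and at 1 and 3 months, with baseline covariates, is used for the missing 6-month GOSE, for example by multiple imputation within arm;
- a complete-case analysis and an analysis that departs from missing at random are reported as sensitivity analyses.

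The first two statements and the retention of collected GOSE are the essential part. The choice of imputation model can be left to the analysis plan.

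The cost is a short protocol amendment and slightly more analysis work. The main analysis would rest on a missing-at-random assumption, which the second sensitivity analysis is there to test.
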